#### 3.2.2. Exclusion Criteria

- 1) Severe Illness or disease, that confound the study results (assessed from the investigators)
- 2) Suspected allergy to trial products (FGM sensor)
- 3) Addiction to alcohol
- 4) Use of drugs
- 5) Mental incapacity

#### 3.2.3. Subgroup

In addition to the subjects with type 1 diabetes, 10 healthy volunteers will participate in this trial. Therefore, placement of Freestyle Libre and application of ECG will be performed before the running competition. After finishing the running competition both devices will be removed by the study personnel.

### 3.3. Cardio-pulmonary Exercise (CPX) Test

Participants will perform a cardio-pulmonary exercise (CPX) test on the track until maximum exhaustion. At the beginning of the test, participants sit quietly on a chair (3 min) before they start to run with 6 km/h. Velocity increases then every 200 m by 0.5 km/h until maximum exhaustion.

Finally, 3 min active recovery at “walking speed” will be performed followed by 3 min sitting passive recovery. VT1, VT2, H RTP, maximum physiological markers and maximal velocity ( $V_{max}$ ) will be used as markers of submaximal and maximal performance capacity.

### 3.4. Pre-exercise Insulin Administration and Carbohydrate Intake Recommendations

Participants will be informed by an information sheet to eat  $\geq 5 - 7$  (g CHO  $\cdot \text{kg}^{-1} \text{day}^{-1}$ ) for the competition preparation period [12]. Insulin doses and carbohydrate amounts will be documented in the FGM system. Participants are told to apply their normal insulin doses or small reductions in bolus insulin (by 25%) during the intervention and document hypoglycaemic events (below 3.9 mmol/l) and additional eaten carbohydrates to counteract hypoglycaemia as well as hyperglycaemic episodes ( $>13.9$  mmol/l) when they inject correction insulin. If hypoglycaemic episodes occurred frequently, additionally basal insulin can be reduced by up to 25%; however, basal insulin reductions need to be discussed in advance with the study physician.

For CPX testing and the individual exercise sessions, participants should consume the last pre-exercise meal at least 2 h before exercising to avoid drastic glucose decreases caused by bolus insulin injection. If the blood glucose is below 7 mmol.l immediately before the exercise, 15–30 g carbohydrates will be supplemented; in contrast to when the blood glucose is 10 mmol.l or above, carbohydrate feeding during exercise will be delayed until reaching 7 mmol.l. When blood glucose decreases during exercise below 7 mmol.l, again 15 g carbohydrates will be supplemented [12]. At each CPX visit, insulin therapy as well as the training concept will be discussed and in case recommendations will be individualised.

Before the competition, participants will reduce the last bolus insulin by 25-75% (when CSII basal rate will be reduced 90 min before the start of competition by 50-80%) depending on the distance they will be running (5 km, 10 km, 21 km or 42 km) [6]. Participants taking along 180 g carbohydrates (5 glucose gels) during the competition and consume further carbohydrates as often as needed to stay within a eu-glycaemic range. Afterwards carbohydrate intake will be calculated by means of consumed gels and additional carbohydrates.

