### 3.5. Measurements

#### 3.5.1. Measurements during CPX

Pulmonary gas exchange variables will be collected continuously during CPX testing by breath-by-breath measurement and averaged over 5 seconds. Heart rate will be measured continuously via chest belt telemetry during all tests and also averaged over 5 seconds. A 3-lead ECG will be obtained in all tests for cardiac monitoring. Capillary blood lactate and blood glucose taken from the earlobe will be measured at the rest, after the last exercise step at the end of the active recovery and finally, at the end of the passive recovery (Biosen S-line, EKF Diagnostics, GER) [9]. Additionally, glucose will be monitored via FGM and glucometer before the start of the CPX testing to avoid exercise-induced hypoglycaemia.

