### 3.7. Secondary endpoints

- Time spent in glycaemic ranges (hypoglycaemia <3.9 mmol/l, euglycaemia 3.9 mmol/l to 10 mmol/l, hyperglycaemia >10 mmol/l) from screening visit to pre-competition visit
- Numbers of hypoglycaemic episodes from screening visit to pre-competition visit
- Glycaemic variability from screening visit to pre-competition visit
- Difference in cardio-pulmonary variables assessed during CPX testing from screening visit to pre-competition visit
- Time spent in glycaemic ranges (hypoglycaemia <3.9 mmol/l, euglycaemia 3.9 mmol/l to 10 mmol/l, hyperglycaemia >10 mmol/l) during the competition depending on therapy adaptation
- Relationship of exogenous insulin and carbohydrate administration strategies and glycaemic variability during running competition
- Numbers of glycaemic episodes during the competition depending on therapy adaptation
- Glycaemic variability during the competition depending on therapy adaptation

|                                                                                  |                |                          |                  |                                                                                     |
|----------------------------------------------------------------------------------|----------------|--------------------------|------------------|-------------------------------------------------------------------------------------|
| [figure not shown] | Title: ExGlyCo | Protocol No: Version 2.1 | Date: 07/10/2019 | [figure not shown] |
|----------------------------------------------------------------------------------|----------------|--------------------------|------------------|-------------------------------------------------------------------------------------|

- Relationship of competent performance and physiological demands

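### The pre-exercise carbohydrate rule in section 3.4 treats every glucose reading below 7 mmol/l alike, including hypoglycaemia below 3.9 mmol/l, and requires no delay or recheck before a CPX test or training session

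*Protocol*

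**What the plan says.** The rule stands in the second paragraph of Protocol section 3.4, whose scope is set by its first sentence: "For CPX testing and the individual exercise sessions, participants should consume the last pre-exercise meal at least 2 h before exercising". Three glucose instructions follow.

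- **Before exercise, below 7 mmol/l:** "immediately before the exercise, 15–30 g carbohydrates will be supplemented". The first four words complete the condition, so they say when glucose is read. No interval between the carbohydrate and the start is given.
- **Before exercise, 10 mmol/l or above:** carbohydrate feeding during exercise waits until glucose reaches 7 mmol/l.
- **During exercise:** "When blood glucose decreases during exercise below 7 mmol.l", a further 15 g is given.

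The same section asks participants to "document hypoglycaemic events (below 3.9 mmol/l) and additional eaten carbohydrates to counteract hypoglycaemia". Section 3.7 uses the same cut-off for its time-in-range endpoints: "hypoglycaemia <3.9 mmol/l, euglycaemia 3.9 mmol/l to 10 mmol/l, hyperglycaemia >10 mmol/l".

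For the CPX test, section 3.5.1 adds that "glucose will be monitored via FGM and glucometer before the start of the CPX testing to avoid exercise-induced hypoglycaemia". It also schedules a resting sample: "Capillary blood lactate and blood glucose taken from the earlobe will be measured at the rest". Section 3.3 describes the test as a run to maximum exhaustion.

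**The concern.** The protocol sets numeric glucose actions and has its own definition of hypoglycaemia, but its pre-exercise rule does not use that definition. A participant at 3.2 mmol/l and one at 6.9 mmol/l receive the same written instruction. Before the CPX test glucose is read with the stated aim of avoiding exercise-induced hypoglycaemia, yet no value is named at which the test waits.

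What is at stake is participant safety. A low may be treated with 15–30 g carbohydrate, and nothing in the text then requires confirmation that it has resolved before a maximal run or a training session. A statistical analysis plan would not supply such a rule, so its absence here cannot be put down to that document being unavailable.

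**Working it through.** There is no figure in the plan to reproduce. The check is a reading of every place where a start level could stand, followed by a count of the occasions the rule governs.

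**1. Overlap of the bands.** The rule applies to all glucose below 7 mmol/l. By the protocol's own cut-offs this range holds two different states:

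| Reading before exercise | Protocol's class | Written action |
|---|---|---|
| below 3.9 mmol/l | hypoglycaemia | 15–30 g carbohydrate |
| 3.9 to below 7 mmol/l | euglycaemia (lower part) | 15–30 g carbohydrate |

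The range 15–30 g leaves room to give more at lower values, but no scaling is stated.

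**2. Search for a start level.**

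- Section 3.1 (investigation plan): mentions therapy strategies given to participants; no glucose value for starting.
- Section 3.2.2 (exclusion criteria): none.
- Section 3.3 (CPX test): 3 min sitting, then running from 6 km/h; none.
- Section 3.4: carbohydrate actions at 7 and 10 mmol/l; documentation of events below 3.9 mmol/l; none for starting.
- Section 3.5.1: two sources of a pre-start reading (FGM and glucometer, then capillary at rest); none.

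**3. What the existing safeguards do.**

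- The meal rule of at least 2 h acts before the start and lowers the chance of a fall caused by bolus insulin. It does not address a reading that is already low.
- FGM wear from screening makes a reading available before any session, but no action beyond the carbohydrate rule is tied to it.
- Basal insulin may be reduced by up to 25% when hypoglycaemia is frequent, after discussion with the study physician. This acts on recurrence, not on the reading at hand.
- Advice is reviewed at visits: "At each CPX visit, insulin therapy as well as the training concept will be discussed and in case recommendations will be individualised". No start level is named as part of that review.
- The 15 g rule acts after the start. During the CPX test, section 3.5.1 lists no capillary glucose between rest and the last exercise step.

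Together these reduce the risk. None of them requires a hypoglycaemic participant to wait.

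**4. Occasions governed by the rule.** Section 3.1 plans 3 CPX tests per participant and section 5 expects approximately 6–10 participants with type 1 diabetes:

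- lower end: 3 × 6 = 18 tests
- upper end: 3 × 10 = 30 tests

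The 10 healthy volunteers of section 3.2.3 are left out, because only the competition is described for them. Training sessions come on top; the protocol does not give their number. The 18 to 30 are all planned tests, not tests expected to begin below 3.9 mmol/l. The document gives no frequency for that.

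**The case against.** The strongest reply is that silence is not permission. Section 3.4 says carbohydrate is given; it does not say that exercise then begins at once. The pre-test check in section 3.5.1 has the stated purpose of avoiding hypoglycaemia, and the trigger of 7 mmol/l already lies 7 − 3.9 = 3.1 mmol/l above the hypoglycaemia cut-off. The study observes people who had already planned to race, the section is headed as recommendations, and these may be individualised. The information sheet or therapy strategies given to participants may contain a start level.

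Much of this stands, and it rules out stronger readings. A reader might infer that the protocol instructs participants to exercise while hypoglycaemic, or straight after eating the carbohydrate. The text supports neither, since the timing words belong to the reading and no interval to the start is stated. A reader might also infer that lows before exercise are left without safeguards; those listed above show otherwise. Nor does the document support a claim that HbA1c, fructosamine or time in range would be distorted.

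What does not stand is the conclusion that nothing needs changing. The competition is the participants' own plan, but the CPX tests are study procedures and the carbohydrate rule is issued by the study. Having set a numeric rule for the whole range below 7 mmol/l, the protocol includes the hypoglycaemic band without handling it separately. A handout might close the gap, but the protocol neither states a start level nor refers to one.

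**Conclusion.** The point holds as a minor participant-safety finding. One instruction covers hypoglycaemia and the lower part of euglycaemia, and neither it nor the pre-CPX checks require a delay or recheck. The text does not direct a start below 3.9 mmol/l; it fails to prevent one.

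Its reach is 18 to 30 maximal tests plus an unknown number of training sessions, with an unknown and unclaimed frequency of low readings. The conclusion rests on two assumptions. One is that the handouts, which are not shown, do not already set a start level; if they do, only the protocol wording needs aligning. The other is the clinical judgement that exercise should not begin while glucose is in the protocol's own hypoglycaemic range. The change is worth making because it is cheap and specific, not because harm has been quantified.

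**What to change.** Add to section 3.4 and to the information sheet:

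*A CPX test or training session is not started at a glucose below 3.9 mmol/l. The low is treated first, and exercise starts only after a recheck at or above 3.9 mmol/l, or at or above a higher level set by the study physician.*

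Keep the 15–30 g rule for 3.9 to below 7 mmol/l and the 15 g rule during exercise as they are. For the CPX test, apply the sentence to the readings already planned in section 3.5.1. The resting capillary value may serve as the recheck if its result is known before the run begins.

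The cost is one sentence in two places, one extra FGM, glucometer or capillary reading when a low is found, and an occasional test or session delayed or rebooked. For training sessions the recheck is a new step, because section 3.4 foresees only one reading before the start.

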### 3.5. Measurements

#### 3.5.1. Measurements during CPX

Pulmonary gas exchange variables will be collected continuously during CPX testing by breath-by-breath measurement and averaged over 5 seconds. Heart rate will be measured continuously via chest belt telemetry during all tests and also averaged over 5 seconds. A 3-lead ECG will be obtained in all tests for cardiac monitoring. Capillary blood lactate and blood glucose taken from the earlobe will be measured at the rest, after the last exercise step at the end of the active recovery and finally, at the end of the passive recovery (Biosen S-line, EKF Diagnostics, GER) [9]. Additionally, glucose will be monitored via FGM and glucometer before the start of the CPX testing to avoid exercise-induced hypoglycaemia.

#### 3.5.2. Measurement of Glycaemic Control

HbA1c and Fructosamine will be collected from the antecubital vein at the before mentioned timepoints. Blood samples (15 ml) will be obtained from a cubital vein and analysed via ELISA (enzyme-linked immunosorbent assay) by the Medical University of Graz, AUT. Glycaemic ranges will be evaluated via interstitial glucose obtained from FGM during the training period and competition.

### 3.6. Primary Endpoint

- Difference in HbA1c and Fructosamine from screening visit to last visit

### 3.7. Secondary endpoints

- Time spent in glycaemic ranges (hypoglycaemia <3.9 mmol/l, euglycaemia 3.9 mmol/l to 10 mmol/l, hyperglycaemia >10 mmol/l) from screening visit to pre-competition visit
- Numbers of hypoglycaemic episodes from screening visit to pre-competition visit
- Glycaemic variability from screening visit to pre-competition visit
- Difference in cardio-pulmonary variables assessed during CPX testing from screening visit to pre-competition visit
- Time spent in glycaemic ranges (hypoglycaemia <3.9 mmol/l, euglycaemia 3.9 mmol/l to 10 mmol/l, hyperglycaemia >10 mmol/l) during the competition depending on therapy adaptation
- Relationship of exogenous insulin and carbohydrate administration strategies and glycaemic variability during running competition
- Numbers of glycaemic episodes during the competition depending on therapy adaptation
- Glycaemic variability during the competition depending on therapy adaptation

|                                                                                  |                |                          |                  |                                                                                     |
|----------------------------------------------------------------------------------|----------------|--------------------------|------------------|-------------------------------------------------------------------------------------|
| [figure not shown] | Title: ExGlyCo | Protocol No: Version 2.1 | Date: 07/10/2019 | [figure not shown] |
|----------------------------------------------------------------------------------|----------------|--------------------------|------------------|-------------------------------------------------------------------------------------|

- Relationship of competent performance and physiological demands

#### **4. Data Management and Analyses**

The documentation of data will be performed in a Case Report Form (CRF), FGM and diabetes diary according to Good Clinical Practice (GCP). After all measurements, data will be monitored before database lock. Descriptive statistic will be performed in both, intention to treat and per protocol participant dataset. A statistical analysis plan will be finished before database lock.

#### **5. Sample Size**

As we will collect data on subjects with type 1 diabetes participating in the Graz marathon competition and do not proactively recruit subjects for this non-interventional study, we will include approximately 6-10 subjects, depending on the number of people taking part in the marathon competition this year.

